### Intervention

A licensed acupuncturist with at least 3 years of clinical experience will perform the intervention. The protocol adheres to the Standards for Reporting Controlled Trials in Acupuncture (STRICTA) recommendations (27). Acupuncture will be performed 30 min prior to anesthesia induction. The acupoints Zusanli (ST36) and Baihui (GV20) were selected based on Traditional Chinese Medicine (TCM) theory and prior evidence suggesting their efficacy in regulating inflammatory responses and improving cerebral function, respectively.

Sterile, disposable stainless-steel needles (0.30 mm × 75 mm; Hwato Brand, Suzhou Medical Appliance Factory, China) will be inserted at the bilateral ST36 and GV20. Acupoint localization follows the WHO Standard (28), as detailed in Table 3 and Figure 2. The needles at ST36 will be inserted to a depth of 30–40 mm at a 30–45° angle inward and downward. The needle at GV20 will be inserted to a depth of 10–20 mm at a 15–30° angle posterior and downward. De qi sensation—characterized by soreness, numbness, distension, or heaviness—will be elicited by lifting, thrusting, and twirling the needles. Subsequently, the needles will be connected to an electro-stimulator (HANS-200A, Nanjing Jisheng Medical Co, Ltd) delivering a dilatational wave at 2 Hz. Stimulation will be maintained for 25–30 min. Any acupuncture-related adverse events, such as hematoma, severe pain, dizziness, or needle breakage, will be monitored and recorded.

**Table 3 tab3:** Location of ST36 and GV20.

Location of acupoints for the EA group	
Acupoint	Location
Zusanli (ST 36)	3 cun directly below Dubi (ST35), 1 finger-breadth lateral to the anterior border of the tibia
Bahui (GV 20)	Five cun directly above the midline of the frontal hairline, or at the midpoint of the line connecting the apex of both ears

1 cun (≈20 mm) is defined as the width of the interphalangeal joint of patient’s thumb.

**Figure 2 fig2:**
[figure not shown]
Anatomical location of acupoints for the Electroacupuncture (EA) and Sham Electroacupuncture (SEA) groups. The left panel illustrates the location of Zusanli (ST36) on the lower leg and its corresponding sham point. The right panel illustrates the location of Baihui (GV20) on the head and its corresponding sham point. Red dots indicate the true acupoints used in the EA group, while blue dots indicate the non-acupoints used in the SEA group (located approximately 20 mm lateral to the true acupoints).

Participants in the SEA group will receive a sham intervention. Needles will be inserted 20 mm lateral to ST36 and GV20 to a superficial depth of 3–4 mm without manipulation or elicitation of De qi. Although electrodes will be connected and the stimulator light activated to mimic the active group, no electrical current will be delivered. To ensure blinding integrity, patients in both groups will be informed that they may or may not feel the electrical stimulation.

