### Randomization and blinding

Randomization will be performed by an independent statistician using SPSS software version 26.0, generating a random number sequence to assign participants in a 1:1 ratio to either the EA or SEA group. To ensure a balanced distribution between the two study sites, randomization will be stratified by center utilizing a block randomization method with varying block sizes of 4 or 6. The allocation sequence will be concealed in sequentially numbered, opaque, sealed envelopes, which will be kept in a secure location and opened by the acupuncturist only after the participant has provided informed consent and completed baseline assessments. Given the nature of the intervention, the acupuncturist cannot be blinded to group allocation; however, to minimize bias, this study employs a patient- and assessor-blinded design. Participants will remain blinded to their treatment assignment through the use of a sham procedure with identical device settings (lights and sound), while outcome assessors—including anesthesiologists responsible for intraoperative management and research registrars conducting postoperative delirium assessments—will be strictly blinded to group allocation. Additionally, the statistician performing the final analysis will handle data with coded identifiers to maintain blinding until the analysis is complete, with emergency unblinding permissible only if essential for clinical management of a severe adverse event.

To evaluate the integrity of the blinding procedures, a standardized blinding assessment questionnaire will be administered to all participants immediately following the completion of the intervention. Participants will be required to quantify the intensity of the stimulation sensation—encompassing specific De qi characteristics such as soreness, numbness, distension, or heaviness—and report their perception regarding the nature of the treatment received. The specific details this assessment are presented in Table 2.

**Table 2 tab2:** Questionnaire for the assessment of blinding effectiveness and acupuncture sensation.

Blind Method Assessment Questionnaire
Name:________ Random Number:_________ Date:___________ **Please answer the following questions according to the latest acupuncture experience.**

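### The stated patient-blinding measures do not cover the sight of the leg needles, which are barely inserted in the sham arm; a drape and a common needle base in both arms would remove that cue

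*Protocol article*

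**What the plan says.** **Needle and active depth.** The Intervention section names one needle, in the paragraph on the active arm: "Sterile, disposable stainless-steel needles (0.30 mm × 75 mm; Hwato Brand, Suzhou Medical Appliance Factory, China) will be inserted at the bilateral ST36 and GV20". For the legs it states: "The needles at ST36 will be inserted to a depth of 30–40 mm at a 30–45° angle inward and downward". For the scalp: "The needle at GV20 will be inserted to a depth of 10–20 mm at a 15–30° angle posterior and downward". De qi is elicited by hand, and 2 Hz current follows. On duration: "Stimulation will be maintained for 25–30 min".

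**Sham.** The paragraph below Figure 2 places the needles 20 mm to the side of the two points and inserts them "to a superficial depth of 3–4 mm without manipulation or elicitation of De qi". It continues: "Although electrodes will be connected and the stimulator light activated to mimic the active group, no electrical current will be delivered". It gives no length, angle or means of fixation for the sham needle.

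**Patient blinding.** Randomization and blinding attributes it to the "use of a sham procedure with identical device settings (lights and sound"). The sham paragraph adds that both groups are told they may or may not feel the stimulation. A questionnaire (Table 2) follows the session, and Statistical analysis compares guessed with actual allocation by Cohen's kappa.

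**Timing.** The Abstract and the Intervention section place the session before anesthesia induction.

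**The concern.** The two stated measures deal with how the device looks and sounds, and with what the patient expects to feel. The needles themselves are a third source of information. Two of the three are on the patient's own legs, and he has not yet been anesthetized. In the active arm roughly half of each leg needle is in tissue. In the sham arm, on the natural reading of the text, almost the whole needle stands outside the skin with a lead clipped to it.

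A patient who draws the right conclusion from this is no longer blind. Pain VAS, HADS-A and catheter-related bladder discomfort depend on his own report, so a difference in expectation between arms could enter those comparisons. Delirium is rated by others, but through repeated interviews with the same patient.

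**Working it through.** The article states no figure for exposed needle length, so there is none to reproduce. The check is geometry.

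**Inputs**

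| Input | Value | Source |
|---|---|---|
| Needle length, active | 75 mm | Intervention |
| Depth at ST36, active | 30–40 mm, at 30–45° | Intervention |
| Depth at GV20, active | 10–20 mm | Intervention |
| Depth, sham | 3–4 mm | Paragraph below Figure 2 |
| Needle length, sham | 75 mm | **Assumption**: the only needle named |

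**Step 1. Exposed length = needle length − inserted length**, taking depth along the shaft.

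- Active leg: 75 − 40 = 35 mm to 75 − 30 = 45 mm.
- Sham leg: 75 − 4 = 71 mm to 75 − 3 = 72 mm.
- Difference: 71 − 45 = 26 mm to 72 − 35 = 37 mm.
- Ratio: 71/45 = 1.6 to 72/35 = 2.1.

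The two ranges do not overlap.

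**Step 2. Share inserted.** Active leg: 30/75 = 40% to 40/75 = 53%. Sham leg: 3/75 = 4% to 4/75 = 5%.

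**Step 3. Scalp.** Active GV20: 75 − 20 = 55 mm to 75 − 10 = 65 mm, against 71–72 mm in sham. The gap is smaller and the patient cannot see it, so the point is confined to the legs.

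**Step 4. Does the meaning of depth matter?** If depth is vertical and the angle is to the skin, inserted length = depth / sin(angle). For ST36 that is at least 30 / sin 45° = 42 mm, so at most 75 − 42 = 33 mm is exposed. At the other extreme, 40 / sin 30° = 80 mm exceeds the needle. Giving the sham needle the same angles (the article gives none), at most 4 / sin 30° = 8 mm is inserted, so at least 67 mm is exposed. The smallest gap is then 67 − 33 = 34 mm, larger than the 26 mm in Step 1.

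**Step 5. Does the sham needle's length matter?** Yes, for total exposed length. A 40 mm sham needle (assumed for illustration) would show 40 − 4 = 36 mm to 40 − 3 = 37 mm, inside the active range. A 25 mm needle would show 21–22 mm. The contrast in Step 1 therefore depends on the needle being the same in both arms.

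**Step 6. Cues against stated measures**

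| Cue | Stated measure |
|---|---|
| Device lights and sound | Same in both arms |
| Lead attached | Electrodes connected in both arms |
| Feeling current or not | Same statement to both groups |
| Sight of the leg needles | None stated |

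**The case against.** Much of the case on the other side stands.

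- **The sham needle length is not stated.** The 75 mm figure appears only for the active arm. The same-needle reading is natural, but it remains a reading, and Step 5 shows that the size of the contrast depends on it.
- **This is a condensed article.** Draping and fixation may be set out in a fuller protocol. Silence on them is not counted as an error here. The point is that the measures the article does name leave one cue uncovered, and that covering it is cheap.
- **Each patient sees only one arm, once.** The ratio of 1.6 to 2.1 compares needles that no patient sees side by side. Appearance informs mainly those who know how deep needling looks. Table 2 asks about earlier acupuncture and electroacupuncture, so such patients are expected.
- **Stronger cues exist.** Active patients are needled with lifting, thrusting and twirling, feel De qi and receive current. Sham patients have none of these, and a drape does not change that.
- **The primary outcome has blinded raters, and blinding is checked.** Both limit the damage. The check, however, comes after the session: it can reveal a failure but cannot prevent one.

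A reader might go further and infer that sham needles will droop or fall out, giving a delivery failure in one arm. The documents give no lead weight, sham angle or record of dislodgement, so that is only a mechanical guess. A reader might also infer that patient blinding rests on lights and sound alone. It does not: the sham includes real skin penetration, connected electrodes and the shared statement about sensation.

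**Conclusion.** The point holds as a minor, optional improvement. As described, sham leg needles are inserted 3–4 mm and active ones 30–40 mm, in patients not yet anesthetized, and neither stated patient-blinding measure covers what the patient can see. With a 75 mm needle in both arms, 71–72 mm is exposed against 35–45 mm.

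This rests on three assumptions: the sham uses the named needle, the legs are in the patient's view, and the session takes place before induction. On the last, Table 1 marks the intervention under the column for the operation, but the Abstract and the Intervention text both put it before induction, and I follow the text.

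The documents do not support saying that patient blinding fails or that the delirium result is biased. The likely effect is on the self-reported secondary outcomes, chiefly in patients with acupuncture experience, and its size cannot be estimated from the article.

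**What to change.** In both arms, drape or screen the lower legs from the patient's view from before the first needle goes in until after the last is removed. Secure every needle and lead with the same adhesive base. Leave sham depth and sites as they are. This works whatever length of sham needle is in use.

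**Cost.** A drape, adhesive bases and a sentence in the protocol.

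**Downside.** Enrollment began in March 2025 and is expected to run to July 2026, so patients already treated had the procedure as now described. Record the date of the change at each center and report the blinding results before and after it. Because allocation is in blocks of 4 or 6 within center, a change by date falls almost equally on the two arms: they can differ by at most 3 patients per center at the switch. The between-arm comparison is therefore not distorted.

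**Limit.** The De qi and current cues remain, so the blinding results should still be read with those in mind.

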### Anesthesia and perioperative management

Upon admission to the operating room, standard monitoring will be established, including electrocardiogram (ECG), heart rate (HR), pulse oxygen saturation (SpO2), and invasive blood pressure (IBP) via radial artery catheterization. Pre-oxygenation will be performed with 100% oxygen at 6 L/min. Anesthesia induction will be achieved via intravenous bolus injections of propofol (1–3 mg/kg), sufentanil (0.3–0.5 μg/kg), and rocuronium bromide (0.6–1 mg/kg). Following loss of consciousness and muscle relaxation, tracheal intubation will be performed by the attending anesthesiologist.

Anesthesia maintenance will be sustained with a continuous infusion of propofol (3–12 mg/kg/h) and remifentanil (0.1–0.3 μg/kg/min). Mechanical ventilation will be adjusted to maintain an end-tidal carbon dioxide (EtCO2) level of 35–45 mmHg. The administration of muscle relaxants (rocuronium) will cease approximately 30 min before the anticipated end of surgery. Additional sufentanil (0.1–0.2 μg/kg) and vasoactive medications will be administered as necessary to maintain hemodynamic stability. Additionally, at the end of the surgery, local anesthetic wound infiltration will be routinely performed by the surgeon at the trocar sites to optimize postoperative analgesia. After surgery, patients will be transferred to the post-anesthesia care unit (PACU). Postoperative pain management will be initiated using patient-controlled intravenous analgesia (PCIA) with sufentanil (concentration adjusted to deliver ~1 μg/kg total dose over the initial period, with a background infusion of 2 mL/h), supplemented by a bolus dose of 1.5 mL with a lockout interval of 15 min.

To minimize confounding factors associated with POD, several key perioperative variables will be strictly controlled. The depth of anesthesia will be monitored continuously using the Bispectral Index (BIS), targeting a range of 40–60. Core body temperature will be monitored via a nasopharyngeal probe, and forced-air warming systems will be utilized to maintain intraoperative normothermia (≥36.0 °C). Hemodynamics will be managed to keep the mean arterial pressure within 20% of the patient’s baseline value.

### Criteria for discontinuing or modifying allocated interventions

Based on the principles outlined in the Declaration of Helsinki (29), participants have the right to withdraw from the study at any stage and for any reason. Discontinuation of Intervention: The study intervention (EA or SEA) will be permanently discontinued under the following conditions:

1) Occurrence of severe adverse events (SAEs) related to the intervention (e.g., severe hematoma, infection, or needle breakage);2) Vasovagal response (e.g., severe dizziness, syncope) during acupuncture;3) Sudden hemodynamic instability (e.g., significant hypotension or arrhythmia) prior to anesthesia induction;4) The participant requests to stop the intervention.

Modification of Intervention: If a participant experiences intolerance or discomfort (e.g., sharp pain) due to the electrical stimulation, the acupuncturist will first adjust the needle depth or reduce the current intensity to a tolerable level. If the discomfort persists despite adjustment, the stimulation will be ceased.

Data Collection for Discontinued Participants: For participants who discontinue the intervention but do not withdraw consent for data collection, follow-up assessments will continue as scheduled. Their data will be included in the final analysis based on the Intention-to-Treat (ITT) principle. For participants who withdraw consent for the entire study, no further data will be collected, but data obtained prior to withdrawal will be retained for safety analysis.

### Provisions for post-trial care

Following the completion of surgery, patients will be transferred to the PACU and subsequently to a general ward or ICU as clinically indicated. All participants will receive standard postoperative care provided by a multidisciplinary team comprising surgeons, anesthesiologists, and critical care specialists, regardless of their group allocation. In the specific event of harm or SAEs proven to be directly related to the study intervention (e.g., acupuncture-associated infection or injury), the research team is committed to providing the necessary medical treatment free of charge, in accordance with applicable laws and insurance policies. Throughout the postoperative period, investigators will conduct regular follow-up visits to closely monitor patient safety, detect potential complications, and provide timely clinical interventions. These visits also serve to address any participant concerns and ensure continuous medical support until discharge.

### Outcomes

#### Primary outcome

The primary outcome measure is the incidence of POD within the first three postoperative days. Assessments will be conducted by trained research registrars who are blinded to group allocation. The evaluation schedule commences 6 h after surgery and continues twice daily (between 08:00–10:00 and 16:00–18:00) from postoperative day 1 through day 3, or until discharge. At each assessment, the level of consciousness will first be screened using the Richmond Agitation-Sedation Scale (RASS). If the score is less than −3, assessment ceases, and the patient is documented as comatose. For patients with a RASS score of ≥ − 3, delirium will be evaluated using the 3-Minute Diagnostic Interview for CAM (3D-CAM) for ward patients, or the Confusion Assessment Method for the ICU (CAM-ICU) for those in the intensive care unit. The 3D-CAM employs CAM scale, comprising 22 items covering four diagnostic features: (1) acute fluctuations in mental status, (2) inattention, (3) disorganized thinking, and (4) altered level of consciousness. A positive diagnosis necessitates fulfilment of both (1) and (2) criteria, alongside at least one of (3) or (4) (30, 31). Any positive assessment during the observation period will be recorded as an incidence of POD.

#### Secondary outcome

1) Number of POD episodes: A positive 3D-CAM assessment will indicate the presence of a POD episode. Transition from POD to non-POD status will be established with two consecutive negative 3D-CAM assessments.2) Onset time and duration of delirium: Onset time of delirium will be defined as the duration from the subject’s return to the surgical ward to the initial delirium diagnosis. Duration of delirium will include the period from the subject’s delirium diagnosis to the occurrence of two negative 3D-CAM assessments. The longest duration of delirium will be recorded for patients experiencing multiple episodes.3) Delirium severity score: Patients with confirmed delirium will undergo assessment for delirium severity utilizing the Confusion Assessment Method-Severity (CAM-S) (32), with daily maximum scores documented. The CAM-S scale comprises four items, yielding a total score of 7 points. Severity grading includes absent (0), mild (1), or marked (2), with a total score of 0 indicating normalcy, 1 signifying mild delirium, 3–5 indicating moderate delirium, and 6–7 representing severe delirium.4) Subtypes of delirium: Delirium subtypes—hyperactive, hypoactive, and mixed—will be determined based on clinical manifestations. RASS will be utilized to classify delirium subtypes, with hyperactive delirium characterized by consistently positive RASS scores (+1 to +4), hypoactive delirium denoted by consistently neutral or negative RASS scores (−3 to 0), and mixed delirium indicated when both positive and neutral/negative RASS scores are observed.5) Pain scores: Postoperative pain at rest will be assessed using the Visual Analog Scale (VAS) during the scheduled afternoon assessment window (16:00–18:00) on postoperative days 1–3.6) Opioid consumption: Opioid consumption, including PCIA and rescue analgesics, will be quantified on postoperative days 1 and 2. Opioid consumption will be converted to a “morphine equivalent dose” for analysis.7) Blood test indexes: Venous blood samples (5 mL) will be collected at three time points: baseline (before acupuncture intervention/anesthesia induction), the end of surgery and postoperative day 1. Plasma levels of S100β and P-tau 217 proteins will be quantified via enzyme-linked immunosorbent assay (ELISA).8) Incidence and severity of catheter-related bladder discomfort (CRBD): CRBD severity will be graded on a scale of 1 to 4, ranging from no discomfort to severe discomfort, with corresponding descriptions provided.9) Perioperative anxiety score: Perioperative anxiety will be measured using the Hospital Anxiety and Depression Scale-Anxiety (HADS-A) subscale (33), assessing the incidence of perioperative anxiety from the day of surgery through 3 days postoperatively. The HADS-A consists of seven items and is a commonly used self-assessment scale for evaluating psychological distress in non-psychiatric patients, demonstrating good sensitivity and specificity. Patients with a HADS-A score of eight or above will be considered to have an anxiety disorder.10) Adverse events: Safety endpoints include general postoperative complications (e.g., cardiac arrhythmias, hypotension, cardiogenic shock) and intervention-related adverse events specific to acupuncture (e.g., subcutaneous hematoma, needle site pain, dizziness/fainting, or needle breakage).

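### The CAM-S rule grades four items 0–2 but gives a total of 7; four such items sum to 8, and a score of 8 has no severity band (minor)

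*Protocol article*

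**What the plan says.** The scoring rule is in the Protocol article, Secondary outcome, item 3 (delirium severity score).

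- Who is scored: "Patients with confirmed delirium will undergo assessment for delirium severity utilizing the Confusion Assessment Method-Severity (CAM-S".
- What is recorded: the score is kept "with daily maximum scores documented".
- Number of items and total: "The CAM-S scale comprises four items, yielding a total score of 7 points".
- Grades: "Severity grading includes absent (0), mild (1), or marked (2". No item is given a different range.
- Bands: "with a total score of 0 indicating normalcy, 1 signifying mild delirium", then "3–5 indicating moderate delirium, and 6–7 representing severe delirium".

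The Primary outcome section restricts which score patterns a delirious patient can have: "A positive diagnosis necessitates fulfilment of both (1) and (2) criteria, alongside at least one of (3) or (4".

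**The concern.** The article prints a scoring rule whose parts do not agree. Either the item grading or the total is wrong, or one item's narrower range has been left out. Someone scoring from this text could reach a total that the scale is said not to have and that no band covers.

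The stake is the severity score itself and the line between moderate and severe. A one-point difference at 5 versus 6 changes the label. Under the diagnostic rule, as the working shows, this is the only band boundary that a scored patient can cross. Severity is also one of the secondary endpoints named in the abstract.

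**Working it through.** **Inputs.** From Secondary outcome, item 3: four items; grades 0, 1, 2; total 7; bands 0, 1, 3–5, 6–7. From Primary outcome: delirium needs features 1 and 2, plus 3 or 4. From Sample size: assumed incidence 20% versus 8%. The group size is 106 per arm.

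**1. The stated total.** Maximum = items × top grade = 4 × 2 = 8. The article's 7 is not reproduced.

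**2. What would give 7.** With item maxima of 1 or 2, a sum of 7 needs exactly one item limited to 0–1: 1 + 2 + 2 + 2 = 7. Any of the four items could be the limited one, and the article does not identify it.

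**3. Patterns open to a scored patient.** Assumption: the four CAM-S items are the four CAM features, and a feature is present when graded 1 or more. Features 1 and 2 each take 1 or 2 (2 × 2 = 4 combinations). Features 3 and 4 take 0–2 but not both 0 (9 − 1 = 8 combinations). That gives 4 × 8 = 32 patterns. Their literal totals are:

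| Total | 3 | 4 | 5 | 6 | 7 | 8 |
|---|---|---|---|---|---|---|
| Patterns | 2 | 7 | 10 | 8 | 4 | 1 |

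So 2 + 7 + 10 = 19 are moderate, 8 + 4 = 12 are severe, and 1 has no band. The minimum is 3, so the normal and mild bands cannot occur in a scored patient. The same holds for a score of 2, which also has no band.

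**4. Literal grading against a 0–7 scale.** The excess is one point wherever the limited item is graded 2.

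| Limited item | One point too high | Moderate (5) → severe (6) | Severe (7) → 8, no band |
|---|---|---|---|
| Feature 1 or 2 | 16 of 32 | 5 | 1 |
| Feature 3 or 4 | 12 of 32 | 4 | 1 |

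Checks:
- Feature 1 limited: feature 1 = 2 leaves 2 × 8 = 16 patterns. A literal 6 needs the other three to sum to 4: feature 2 = 1 with features 3 + 4 = 3 (2 ways), or feature 2 = 2 with features 3 + 4 = 2 (3 ways), total 5.
- Feature 3 limited: feature 3 = 2 leaves 4 × 3 = 12 patterns. A literal 6 needs features 1 + 2 + 4 = 4: (1,1,2), (1,2,1), (2,1,1) or (2,2,0), total 4.

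The direction is the same whichever item is limited.

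**5. How many patients are scored.** 0.20 × 106 + 0.08 × 106 = 21.2 + 8.48 = 29.68, about 30 of 212 at the planned rates.

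**The case against.** The strongest reply is that this is a compressed description of a published, cited instrument. The grading sentence says that the grades include 0, 1 and 2; it does not say that each item carries all three. The total and the top band agree on 7, so a reader may suppose that one item's narrower range was left out and that the instrument or the CRF supplies it. This stands in part: the text may be incomplete rather than wrong in intent. It does not remove the contradiction, because the article prints grades, item count and total together and they do not reconcile without a limit that it never states.

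Four stronger readings are tempting, and the documents do not support them.

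- **That the limited item is acute change or fluctuation.** The article does not identify the item, which is why a range is given rather than the feature 1 figures alone.
- **That a moderate-versus-severe comparison will be distorted.** Statistical analysis names no analysis of the severity categories; the score falls under the general provision for other secondary outcomes.
- **That assessors or centres score differently, or that the treatment comparison is biased.** No differing practice is shown. Data collection and management provides standardised training in the outcome tools, although it singles out the 3D-CAM. Assessors are blinded, so no differential error between arms is shown.
- **That misgraded forms exist and need recoding.** Enrolment has begun, but no completed form is in evidence.

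**Conclusion.** The point holds as a minor internal contradiction. That the grades sum to 8 against a stated 7, and that 8 has no band, follows from item 3 alone.

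The claim that literal scoring would be too high rests on 7 being the intended maximum, which the total and the top band both support. If 8 were intended, nothing would be over-scored; the total would be wrong and the top band would stop one point short. The pattern counts (12 or 16 of 32 one point high, 4 or 5 crossing into severe, 1 reaching 8) further assume that the CAM-S items are the four CAM features and that the literal grading is used. They count possible patterns, all weighted equally, and say nothing about how many patients would be affected.

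The reach is limited to one secondary outcome in about 30 patients at the planned rates. The primary outcome and the sample size do not depend on it.

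**What to change.** - In Secondary outcome, item 3, state item ranges that sum to 7: three items 0–2 and one item 0–1, with the limited item named from the cited instrument.
- Print the same ranges on the CRF and set a 0–7 range check on the total. Check the items as well: a check on the total alone would catch only the all-marked pattern and would miss a 6 that should be a 5.
- Before analysis, check completed forms against those ranges and correct only those found out of range.

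The cost is one sentence, a CRF and database range check, and a short review of the forms of delirious patients. Nothing in the design, the primary analysis or the sample size changes.
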